## Abstract

Supplemental Digital Content is available in the text

## Introduction

1

Cold hypersensitivity in the hands and feet (CHHF) is a condition of thermal hyperalgia in which patient feels a sense of coldness in the extremities to a greater extent than unaffected people in any environment, with worsening discomfort at lower temperatures.^[1]^ CHHF patients mostly complain of discomfort when working with their hands, and a low quality of life due to the inconvenience of wearing socks or gloves in hot weather.^[2]^ It is mostly diagnosed by patient's subjective symptoms and experiences, which has no clear conception in Western medicine.^[3]^ According to a previous observational study, cold hypersensitivity is frequent in Asians, particularly among females compared to males with an approximate ratio of 3:2.^[4]^

In Korean medicine, CHHF is considered a treatable symptom that is caused by 3 types of pathogens. First, there is an invasion of pathogens that cause a cold through external pathogenic factors, affecting the whole body. The other is the disharmony of specific internal organs, such as deficiency of spleen yang, kidney yang, blood, or Qi. The last is the concurrent occurrence of cold and heat syndrome due to the lack of stomach harmony and adverse Qi.

Ucha-Shinki-Hwan (UCHA) is a frequently prescribed herbal formula by East Asian medicine practitioners, mostly in Korea, Japan, and China.^[5]^ It is mentioned in a medical book called Ji- sheng Fang (A Book of Formulas to Promote Well-Being), written in the 13th century by Master Yan.^[6]^ It is used to treat kidney deficiency syndrome and lower limb dysfunction by balancing Yinyang and removing dampness and turbidity. Previous research has reported that it has beneficial effects in various diseases including chemotherapy-induced neuropathy with coldness,^[7–9]^ diabetic neuropathy,^[10]^ and overactive bladder.^[11–12]^ Our research team also performed an in vitro study on the inhibitory effect of UCHA on cold-induced response in human dermal microvascular endothelial cells (HDMEC) and observed the inhibitory effects on the contraction of cold-exposed HDMEC by targeting RhoA activation.^[13]^

Although UCHA is typically prescribed in the treatment of various symptoms and concomitant cold extremity, a randomized clinical trial (RCT) has not been performed yet to assess the clinical efficacy of UCHA in the treatment of CHHF. Therefore, this exploratory, randomized, placebo-controlled, double-blind trial aims to evaluate the efficacy and safety of UCHA and to examine the feasibility of a full RCT for the treatment of CHHF in Korean female patients.

## Methods

2

### Objectives

2.1

The aim of this trial is to evaluate the efficacy and safety of UCHA in Korean female patients with CHHF, using an exploratory RCT protocol that includes examination of the severity of CHHF, skin temperature (ST), quality of life, and safety.

### Study design and setting

2.2

This pilot, randomized, double-blind, placebo-controlled, parallel-group, multi-center clinical trial will be conducted in 5 university-affiliated Korean medicine hospitals, namely Gachon University Gil Korean Medical Hospital, Korean Medical Hospital of Sangji University, Semyung University Second Affiliated Korean Medical Hospital at Chungju, Kyung Hee University Korean Medical Center, and Kyung Hee University Korean Medicine Hospital at *Gangdong*.

Written informed consent will be obtained from the subjects, after giving detailed explanation and they will be screened up to 7 days prior to randomization. Once assigned to the subject identifier, they will be administered investigational products (IPs) for 8 weeks and asked to visit the enrolled trial site every 4 weeks for efficacy and safety examination. At 4 weeks after post treatment visit, follow-up visit will be scheduled. The participants will be asked to return any remaining IPs at each visit to monitor adherence, in order to calculate medication compliance. During the trial, the participants will be prohibited from administering any medications which can impact CHHF. The methodology of the trial is based on the consolidated standards of reporting trials guidelines and standard protocol items: recommendations for interventional trials checklist (see additional file 1). Table 3 presents a schematic flow diagram of the study.

### Participants

2.3

#### Inclusion criteria

2.3.1

The inclusion criteria of this study are as follows: patients aged 19 to 59 years who present with CHHF; CHHF score higher than 40 points on the 100-mm visual analog scale (VAS); thermal differences between the palm (PC8) and the upper arm (LU4) may be higher than 0.3°C and differences between anterior of thigh (ST32) and the top of the foot (LR3) may be higher than 2.0°C; symptoms of CHHF in normal temperatures when most individuals do not feel cold or having symptoms of extremely cold hands on cold temperature exposure or individuals who are on the return to a warmer environment but, their cold hands have not completely returned to a normal temperature. Voluntary participation with a signed informed consent form after a detailed explanation of the trial has been obtained.

#### Exclusion criteria

2.3.2

The exclusion criteria of the UCHA trial are provided in Table 1. Volunteers who meet any of the conditions cannot enroll to this study.

**Table 1 T1:**
[figure not shown]
Exclusion criteria of the trial.

#### Participant withdrawal criteria

2.3.3

The trial would be discontinued if participants met any of the criteria summarized in Table 2. The subjects who are withdrawn after randomization will be followed-up for outcomes. Reasons for withdrawal will be documented in case report forms (CRFs) and data will be analyzed using the intention-to-treat (ITT) principle. Each site clinical research coordinator will be responsible for making next visit reminder phone calls to prevent participant dropout.

**Table 2 T2:**
[figure not shown]
Withdrawal criteria of the UCHA study.

**Table 3 T3:**
[figure not shown]
Study flow of the trial.

### Randomization

2.4

Suitable participants, who agree to participate in this RCT, will be randomly assigned to a UCHA group or a placebo group at a 1:1 ratio. A total of 164 eligible participants each will be allocated to the UCHA and placebo groups. An internet-based research randomizer (IRR) developed by the contract research organization (CRO), the Institute of Safety and Effectiveness Evaluation for Korean Medicine (ISEE), will perform the assignment. A random order will be generated by the CRO's independent professional statistician using the R software (The R Foundation for Statistical Computing, Vienna, Austria) and stratified by the hospital using random block sizes of 2 and 4 based on the allocation code provided by the R software.

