#### Sample size calculation

2.8.6

The change in the CHHF VAS score between baseline and post treatment will be used as the primary outcome measure. The hypothesis is follows: 
[figure not shown]

Δ1: Mean change in the CHHF VAS score between baseline and post treatment in the UCHA group

Δ2: Mean change in the CHHF VAS score between baseline and post treatment in the placebo group

Based on the prior research,^[14]^ the expected mean CHHF VAS score difference in the SDT group is 10.93, and the pooled standard deviation (SD) is estimated to be 22.28. Considering a dropout rate of 20%, we determine to recruit 82 subjects per arm to calculate the treatment efficacy and to offer the power calculation for a future large-scale RCT. Each site will recruit the participants competitively.

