##### Efficacy assessment

2.8.7.1

For the efficacy assessment of this trial, both ITT and per-protocol (PP) analyses will be performed. Missing data will be adjusted using the last-observation-carried-forward (LOCF) imputation method on ITT analysis. The continuous variables will be expressed as the mean ± SD and the nominal variables will be reported as percentages. The ITT method will include all randomized subjects, regardless of any protocol violations or trial dropouts. The PP method will include only the subjects who have completed the whole study period without any major protocol violations and who have medication compliance rate equal to or greater than 70%. Missing values from the efficacy analysis will be modulated by applying the LOCF. The baseline demographic information will be compared by either a chi-square test for nominal variables or an analysis of variance (ANOVA) for continuous variables. For the within-group analysis, the primary and secondary outcome variables will be assessed using a paired *t* test. The between-groups analysis after 8 weeks of administration will be performed using a repeated-measure ANOVA for the primary outcome variables, and a paired *t* test for the mean difference in the VAS score between the SDT and placebo groups. As a secondary outcome variable, the mean differences in ST and WHOQOL-BREF scores between the groups will be analyzed using a repeated-measure ANOVA for ST and an ANOVA and post-hoc analysis for the WHOQOL-BREF scores. For all non-normal distribution data, a nonparametric statistical test will be performed. SPSS for Windows version 25.0 (SPSS Inc., Chicago, IL) will be used for statistical analysis. The statistical significance level will be set at *P* < .05.

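### Randomisation is stratified by hospital but no named efficacy analysis includes hospital; to the extent that hospitals differ in the analysed outcome, the tests are mildly conservative

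*Protocol article*

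**What the plan says.** Section 2.2 describes a trial in five hospitals: "multi-center clinical trial will be conducted in 5 university-affiliated Korean medicine hospitals". Under section 2.4, participants "will be randomly assigned to a UCHA group or a placebo group at a 1:1 ratio", and the random order is "stratified by the hospital using random block sizes of 2 and 4". Section 2.8.6 adds that "Each site will recruit the participants competitively", so site sizes are not fixed in advance.

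Section 2.8.7.1 gives the efficacy methods. For VAS: "The between-groups analysis after 8 weeks of administration will be performed using a repeated-measure ANOVA for the primary outcome variables", together with a second "test for the mean difference in the VAS score between the SDT and placebo groups". For the secondary outcomes: "a repeated-measure ANOVA for ST and an ANOVA and post-hoc analysis for the WHOQOL-BREF scores". Non-normal data go to a nonparametric test. Hospital is not named as a factor, covariate or stratum in any of these. The sample size in section 2.8.6 does not use hospital either. That section defines the primary outcome as the change in VAS from baseline to post treatment.

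**The concern.** Blocks of 2 and 4 keep the two arms within two participants of each other at every hospital. Differences between hospitals therefore largely cancel when the arms are compared. A model without hospital does not know this: it leaves hospital differences in its residual variance, so its standard error exceeds the real sampling variability of the estimate.

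The consequence is a nominal 5% test that runs below 5%, confidence intervals that are too wide, and some power given away. What is at stake is precision, not protection against false positives. How much is at stake depends on how far hospitals differ in the quantity actually analysed.

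**Working it through.** **Reproducing the plan's own figure.** Inputs from section 2.8.6: difference 10.93 mm, SD 22.28 mm, dropout 20%, 82 per arm. Section 2.8.7.1 gives the 0.05 level. The article states neither power nor sidedness; 80% and two-sided are assumed.

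n per arm = 2 × [22.28 × (1.960 + 0.842) / 10.93]² = 65.23, which rounds up to 66. With dropout, 65.23 / 0.80 = 81.5, which rounds up to the stated 82. (Rounding to 66 first gives 82.5, so 83.) The figure reproduces.

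**Effect of leaving out hospital.** Let r be the share of the analysed outcome's variance that lies between hospitals. Let s = 22.28 be the total SD and n the number per arm. With balance within hospital:

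- true variance of the difference = 2s²(1 − r)/n
- variance that the unadjusted analysis estimates = 2s²/n
- ratio of unadjusted to true standard error = 1/√(1 − r)
- actual type I error = 2 × [1 − Φ(1.96/√(1 − r))]
- unadjusted power = Φ[(10.93/SE − 1.96)/√(1 − r)], with SE = s√(2/n)
- adjusted power = Φ[10.93/(SE√(1 − r)) − 1.96]

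With n = 66, SE = 22.28 × √(2/66) = 3.878 mm, so the unadjusted 95% half-width is 1.96 × 3.878 = 7.60 mm. The documents do not give r, so a range is shown:

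| r (assumed) | CI too wide by | Actual type I error | Half-width without / with hospital (mm) | Power without / with hospital, 66 per arm |
|---|---|---|---|---|
| 0 | 0% | 5.0% | 7.60 / 7.60 | 80.5% / 80.5% |
| 0.05 | 2.6% | 4.4% | 7.60 / 7.41 | 81.1% / 82.4% |
| 0.10 | 5.4% | 3.9% | 7.60 / 7.21 | 81.7% / 84.4% |
| 0.20 | 11.8% | 2.8% | 7.60 / 6.80 | 83.1% / 88.3% |

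The ITT analysis keeps all randomised participants with LOCF, so 82 per arm is the other relevant count. There SE = 22.28 × √(2/82) = 3.480 mm. Power is 88.7% without hospital against 89.7% with it at r = 0.05, and 89.3% against 91.2% at r = 0.10.

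**Check by simulation.** Set-up: five hospitals, blocks of 2 and 4, 164 participants, even sites or uneven sites (80, 40, 20, 16, 8), and 8,000 null trials per setting (Monte Carlo standard error about 0.0024 near 5%).

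| r | Unadjusted type I error, full follow-up (even / uneven) | Unadjusted type I error, 20% dropout (even / uneven) |
|---|---|---|
| 0.05 | 0.0435 / 0.0452 | 0.0456 / 0.0437 |
| 0.10 | 0.0408 / 0.0395 | 0.0435 / 0.0454 |
| 0.20 | 0.0294 / 0.0254 | 0.0301 / 0.0338 |

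The test with hospital as a fixed effect stayed between 0.047 and 0.054 in every setting. With unstratified randomisation at r = 0.20, the unadjusted test gave 0.048. So the conservatism comes from stratifying and then leaving the stratum out. Uneven site sizes make little difference, and dropout, which loosens the balance, tends to weaken the effect.

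**Which r applies to the primary outcome.** A stable difference between hospitals in how patients score the VAS is present at baseline and at week 8, so it cancels in the change score. It also cancels in a group-by-time test, which uses within-subject error. Only hospital differences in change remain. The article does not say which repeated-measures term is tested; a group main effect on VAS levels would carry the full hospital differences.

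**The case against.** The strongest objection is that section 2.8.7.1 names families of tests and writes out no model. Nothing in it excludes hospital, and an analysis plan that is not shown may add the term. That stands as a limit: a reader might infer that the trial will certainly be analysed without hospital, and the article does not establish this. But the section names a method for each outcome, and as written those methods do not reflect the stratified allocation.

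A second objection is that no planned power is lost. That also stands. Unadjusted power at r = 0.05 or 0.10 (81.1% or 81.7%) is slightly above the 80.5% given by the design at r = 0. What is forgone is a gain, and it shrinks to about 1 or 2 points at 82 per arm.

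A third is that the features suggesting hospital differences are weak for the VAS. A reader might point to the 24 ± 2°C measuring condition in section 2.8.2.1 or to competitive recruitment. The first concerns skin temperature, a secondary outcome, and is itself a standardisation step. The second makes site sizes uneven but does not make hospital means differ. Neither shows that change in VAS differs between hospitals.

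**Conclusion.** The point holds as a modest, conditional one. Allocation is stratified by hospital, the named efficacy analyses have no hospital term, and the direction of any resulting error is conservative.

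Its size rests on r, which is assumed, on 22.28 mm being the total SD, and on a two-sided 5% test. It ranges from nothing at r = 0 to the 5% and 10% rows above. For change in VAS the low end is the more likely. At r = 0.20 the loss would be material, but nothing in the documents supports a value that high.

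A reader might infer that the intervals are definitely too wide, or that the trial's validity is threatened. The documents support neither: they give no between-hospital variance, and the omission causes no bias and no excess of false positives. The case for change is that the improvement is almost free.

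**What to change.** State in section 2.8.7.1 that hospital (five levels) enters as a fixed effect in the between-group models for VAS, skin temperature and WHOQOL-BREF.

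The cost is one line of wording and four degrees of freedom. With 132 evaluable participants, residual degrees of freedom for a two-group comparison go from 130 to 126, and the critical t value moves only from 1.978 to 1.979. Sample size and conduct do not change. Section 3.1 reports 72 participants recruited with recruitment continuing, and section 2.9 places database lock after trial completion, so as of the article the term could still be specified before the data are analysed.

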### Blinding

2.5

Both the researchers and subjects will be blinded to the assigned IP. SHINHWA Pharmaceuticals will package, label the randomization code number on the IP, and distribute to trial sites. Each subject will receive the IRR-assigned IP by independent research pharmacists or assistants who are also blinded to the randomization, in each hospital.

### Procedure

2.6

#### Recruitment

2.6.1

Participants will be recruited from 5 university-affiliated Korean medicine hospitals located in various administrative areas in Korea. Each site will recruit the participants who have voluntarily visited each trial site for enrollment or through public advertising.

#### Study schedule

2.6.2

The items to be measured at each visit are provided in Table 3.

### Interventions

2.7

After randomization, the participants will be prescribed 2.5 g of UCHA or placebo 3 times a day after 30 minutes of each meal for 8 weeks.

UCHA is manufactured by Tsumura Co. (Tokyo, Japan). UCHA granulated extract contains 1.7 g of Rehmannia glutinosa Radix, 1.0 g of Achyranthes bidentata Blume Radix, 1.0 g of Cornus officinalis Fructus, 1.0 g of Dioscorea batatas Decne. Rhizoma, 1.0 g of Plantago asiatica Semen, 1.0 g of Alisma orientale Rhizoma, 1.0 g of Poria cocos Sclerotium, 1.0 g of Paeonia suffruticosa Cortex, 0.3 g of Cinnamomum cassia Cortex, and 0.3 g of Aconitum carmichaelii Tuber. It will be extracted from the raw materials described above and concentrated to 2.5 g per dose.

Placebo is manufactured by SHINHWA Pharmaceuticals (Daegu, Korea). The granulated extract contains 2.25 g of lactose, 0.175 g of dextrin, and 0.075 g of caramel coloring per dose. It has a similar color, shape, weight, flavor, and taste to that of UCHA.

Both IPs are packaged and distributed to trial sites by SHINHWA Pharmaceuticals.

### Outcome

2.8

#### Primary outcome measure

2.8.1

##### VAS

2.8.1.1

The VAS score (ranging from 0 mm as no discomfort to 100 mm as the maximum coldness imaginable) will be used to assess the severity of CHHF at every visit.^[14]^

#### Secondary outcome measures

2.8.2

##### ST: Thermometer measurement

2.8.2.1

After 20 minutes of relaxation at 24 ± 2°C, the ST will be measured by a thermometer (Testo 835-T1, Lenzkirch, Germany) at acupoints PC8, LU4, ST32, and LR3 at visit 2, 3, 4, and follow-up.

##### World Health Organization Quality Of Life Scale Abbreviated Version (WHOQOL-BREF)

2.8.2.2

The Korean version of the WHOQOL-BREF consists of a 26-item questionnaire that measures 5 domains of an individual's quality of life, namely general quality of life; psychological, physical, and environmental health; and social relationships.^[15]^ It will be conducted at visits 2, 4, and follow-up.

#### Safety outcome measure

2.8.3

The safety assessment will be performed for all subjects who have been administered IP at least once. The subjects’ vital signs and general physical condition will be examined at every visit. Hematological examination (white blood cell, red blood cell, hemoglobin, and platelet), blood chemistry test (blood urea nitrogen, creatinine, aspartate aminotransferase, alanine aminotransferase, gamma-glutamyl transpeptidase) will be performed at screening and visit 4. Blood glucose test, thyroid test (free T4 and thyroid-stimulating hormone), urine analysis, and pregnancy test (urine human chorionic gonadotropin) will be conducted at screening visit. The occurrence of adverse events (AEs) will be checked at visit 3, 4, and 5.

#### Compliance calculation

2.8.4

At visit 2 and 3, a bag of IP, which includes 93 aluminum foil packages, will be provided to the subjects. They will be asked to return the remaining investigational medications. The rate of compliance will be calculated as compliance (%) = ([93 - remaining products]/expected intake) × 100. Clinical trials will be continued only if compliance is equal to or greater than 70%.^[16]^

#### AE reporting

2.8.5

The investigators should educate the subjects to inform about any AEs that occur after IP administration. All AEs that occur after the start of this trial should be recorded in the CRF whether or not they are related to the IP and should also be evaluated for causal relationships. In the event of any irregular medical conditions, such as serious AEs, the principal investigator of the site will contact the CRO and sponsors immediately to process the codebreaking in accordance with standard operating procedures (SOPs). They are also required to notify the Institutional Review Board and regulatory authorities within 24 hours.

#### Sample size calculation

2.8.6

The change in the CHHF VAS score between baseline and post treatment will be used as the primary outcome measure. The hypothesis is follows: 
[figure not shown]

Δ1: Mean change in the CHHF VAS score between baseline and post treatment in the UCHA group

Δ2: Mean change in the CHHF VAS score between baseline and post treatment in the placebo group

Based on the prior research,^[14]^ the expected mean CHHF VAS score difference in the SDT group is 10.93, and the pooled standard deviation (SD) is estimated to be 22.28. Considering a dropout rate of 20%, we determine to recruit 82 subjects per arm to calculate the treatment efficacy and to offer the power calculation for a future large-scale RCT. Each site will recruit the participants competitively.

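### VAS is scheduled at two visits before the first dose, but the primary comparison is described with a single baseline and no covariate, so it may leave one reading unused

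*Protocol article*

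**What the plan says.** - **Primary outcome** (Protocol article, Sample size calculation): "The change in the CHHF VAS score between baseline and post treatment will be used as the primary outcome measure". The visible text does not name the visit that supplies the baseline.
- **VAS schedule** (VAS): the scale "will be used to assess the severity of CHHF at every visit".
- **Screening** (Study design and setting): "they will be screened up to 7 days prior to randomization". The Safety outcome measure section treats screening as a visit of its own, with tests that "will be conducted at screening visit".
- **First dispensing** (Compliance calculation): "At visit 2 and 3, a bag of IP, which includes 93 aluminum foil packages, will be provided to the subjects".
- **Entry criterion** (Inclusion criteria): "CHHF score higher than 40 points on the 100-mm visual analog scale (VAS". No visit is named for the qualifying reading.
- **Other outcomes**: skin temperature is read "at acupoints PC8, LU4, ST32, and LR3 at visit 2, 3, 4, and follow-up", and WHOQOL-BREF also starts at visit 2.
- **Analysis** (Efficacy assessment): repeated-measures ANOVA and a t test on the VAS difference between groups, and paired t tests within groups. No covariate is named, and the visits that enter the ANOVA are not listed.

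**The concern.** Taken together, these sections give each participant a VAS at screening and another at visit 2, both available before any product is taken. A single self-rated VAS carries day-to-day noise. When one reading is subtracted to form a change, all of that noise enters the outcome. A second reading taken within about a week carries further information on the patient's underlying level, and the plan as described has no stated use for it.

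What is at stake is precision in a pilot whose results are meant to feed the power calculation of a larger trial. A smaller, separate matter is the within-arm change. If the reading that qualified the patient also served as baseline, both arms would show some fall without any treatment effect, and the planned within-group paired t tests would pick it up.

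**Working it through.** **1. The plan's own figure.** The Sample size calculation gives a difference of 10.93, an SD of 22.28, 20% dropout and 82 per arm. I assume that the SD is that of the change, the test is two-sided at 0.05 and power is 80%.

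n = 2 × [22.28 × (1.960 + 0.842) / 10.93]² = 65.23 per arm. Then 65.23 / 0.8 = 81.5, which rounds up to 82. (Rounding to 66 first gives 66 / 0.8 = 82.5, so 83.) The stated size reproduces.

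**2. Gain from the second reading as a covariate.** Let ρ be the correlation of either pre-dose reading with the week-8 reading, and b the correlation between the two pre-dose readings, with equal variances set to 1. Neither ρ nor b is in the document; both are assumptions.

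- Residual variance with one baseline covariate: 1 − ρ²
- With both: 1 − 2ρ²/(1 + b)

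| ρ | b | one | both | ratio | cut |
|---|---|---|---|---|---|
| 0.4 | 0.8 | 0.840 | 0.822 | 0.979 | 2% |
| 0.5 | 0.8 | 0.750 | 0.722 | 0.963 | 4% |
| 0.5 | 0.7 | 0.750 | 0.706 | 0.941 | 6% |
| 0.6 | 0.6 | 0.640 | 0.550 | 0.859 | 14% |
| 0.5 | 0.9 | 0.750 | 0.737 | 0.982 | 2% |

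In terms of patients, 82 / 0.979 = 84 and 82 / 0.859 = 95. The 14% end needs b = ρ, that is, readings a week apart that agree no better than readings eight weeks apart. Selection at VAS above 40 narrows the spread of the qualifying reading and trims the gain. With an assumed mean of 50 to 65 and SD of 15 to 20, a simulation at ρ = 0.5 and b = 0.7 to 0.8 gives about 3 to 5% instead of 4 to 6%.

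**3. The step from change score to covariate.** The variance of a change from one baseline is 2(1 − ρ). Against it, one baseline covariate gives (1 − ρ²) / [2(1 − ρ)] = (1 + ρ)/2, which is 0.70 to 0.80 for ρ = 0.4 to 0.6. Most of the gain over a plain change score therefore comes from the first covariate; the 2 to 14% is what the second adds.

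**4. Within-arm shift if the qualifying reading were the baseline.** For a normal VAS cut at 40, the expected fall from the qualifying reading to another pre-dose reading is SD × λ × (1 − b), where λ = φ(a)/[1 − Φ(a)] and a = (40 − mean)/SD. This is the extra fall compared with using visit 2.

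- Mean 65, SD 15, b = 0.8: 15 × 0.104 × 0.2 = 0.3 mm
- Mean 50, SD 20, b = 0.6: 20 × 0.509 × 0.4 = 4.1 mm

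For the whole fall to week 8, replace b by ρ. A simulation with mean 60 to 70, SD 15 to 20 and ρ = 0.5 to 0.6 gives 0.3 to 2.9 mm from the qualifying reading and about 0 to 1.1 mm from visit 2. At mean 60, SD 20, ρ = 0.5 and b = 0.7, the falls are 2.9 mm (qualifying reading), 1.1 mm (visit 2) and 2.0 mm (average of the two). The shift is the same in both arms and cancels in the contrast.

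**The case against.** Change from one pre-dose reading is ordinary practice, and a condensed article may leave the choice of baseline visit to the visit table (not shown), the full protocol or the SAP. That stands: the unnamed baseline visit is not itself an error.

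A reader might infer that the qualifying reading serves as baseline and distorts the primary result. The documents do not support this. Product is first dispensed at visit 2, and the two secondary efficacy outcomes have their first listed readings there, so the text points to visit 2. The inclusion criteria do not say at which visit the qualifying VAS is taken. Any regression to the mean is equal in both arms.

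A reader might also infer that precision is certainly lost. The article does not list the visits in the repeated-measures ANOVA, so the screening reading could enter. Entered only as one more time level, however, it would not by itself give the covariate adjustment worked out above.

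Finally, no minimum gap between screening and randomization is stated. If the two visits fall on one day, the second reading adds little. That stands too, and it limits the size of the gain.

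**Conclusion.** The point holds as a modest, nearly free improvement to the analysis. The schedule provides two pre-dose VAS readings, and the described primary comparison names one baseline and no covariate. Using both as covariates cuts residual variance by about 2 to 14% beyond a single baseline covariate. This rests on assumed correlations (ρ of 0.4 to 0.6, b from ρ up to 0.8) and equal variances; mid-range values give about 4 to 6%, or 3 to 5% after allowing for the entry cut.

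The between-group contrast is unbiased and the sample size is sound. Only the within-group changes would be shifted, and only if the qualifying reading were the baseline, by roughly 0.3 to 4 mm under the assumed means, SDs and retest correlations. For scale, the planned difference is 10.93 mm.

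**What to change.** - Analyse week-8 VAS in a between-group model with the screening VAS and the visit 2 pre-dose VAS both entered as covariates.
- Name the visit 2 pre-dose reading as the baseline for the reported within-arm change and the paired t tests.
- Do not subtract the average of the two pre-dose readings instead: it brings back part of the shift that naming visit 2 avoids.

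The cost is a few lines of analysis wording and one further degree of freedom for the second covariate. No visit or measurement is added. The article reports recruitment still under way, with data entry and lock to follow completion, so the wording could be settled before unblinding.

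### Sample size and VAS comparison name an undefined SDT group, 10.93 mm is worded as a one-group difference although 82 per arm reproduces as a between-arm one, and the allocation sentence contradicts 82 per arm

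*Protocol article*

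**What the plan says.** Sections 2.4 and 2.7 of the protocol article describe two arms, UCHA and placebo, allocated 1:1. In section 2.8.6 the hypothesis is set up with Δ1 as the mean VAS change in the UCHA group and Δ2 as the mean change in the placebo group. The planning figures follow, attributed to prior research: "the expected mean CHHF VAS score difference in the SDT group is 10.93, and the pooled standard deviation (SD) is estimated to be 22.28". The size is then fixed: "Considering a dropout rate of 20%, we determine to recruit 82 subjects per arm". Section 2.8.6 gives no power, alpha or sidedness. A significance level appears only in section 2.8.7.1: "The statistical significance level will be set at *P* < .05".

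Section 2.8.7.1 plans a repeated-measures ANOVA for the primary outcome and, beside it, a paired t test for "the mean difference in the VAS score between the SDT and placebo groups".

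Section 2.4 states: "A total of 164 eligible participants each will be allocated to the UCHA and placebo groups".

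**The concern.** Three statements that fix the size and main comparison of the trial do not fit the rest of the text.

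- SDT is not an arm and is not explained. It occurs in both the sample-size section and the analysis section, so it is not a single slip of the pen.
- The hypothesis needs a value for the difference between two mean changes. The text supplies a difference in one group and gives no placebo change. On a subjective VAS some placebo response is plausible. If 10.93 mm were a within-arm change, entering it as the treatment difference would amount to assuming that placebo patients do not change.
- The allocation sentence in 2.4 and the per-arm figure in 2.8.6 differ by a factor of two.

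At stake is how the result will be read. The trial is meant to inform the power calculation of a larger RCT, so a planning effect whose meaning is unclear can carry over into that trial.

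**Working it through.** **Inputs.** Effect 10.93 mm, SD 22.28 mm, dropout 20% and 82 per arm (section 2.8.6); alpha 0.05 (section 2.8.7.1); 1:1 allocation (section 2.4). A two-sided test and 80% power are assumptions made here, since the document states neither.

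**Reproducing 82, with 10.93 as a between-arm difference (two-sample formula).**

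n per arm = 2 × (1.960 + 0.842)² × (22.28 / 10.93)² = 65.23

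65.23 / (1 − 0.20) = 81.5, which rounds up to 82 and matches the plan. Rounding to 66 first gives 66 / 0.8 = 82.5, hence 83, so the exact match depends on when the rounding is done.

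**With 10.93 as a one-group change (one-sample or paired formula), same settings.**

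n = (1.960 + 0.842)² × (22.28 / 10.93)² = 32.6, rounded up to 33

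33 / 0.8 = 41.25, hence 42. This is about half of 82.

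**Other conventional settings, per arm after dropout.**

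| Reading | Sides | 80% | 85% | 90% | 95% |
|---|---|---|---|---|---|
| Two-sample | two | 82–83 | 94 | 110 | 135 |
| Two-sample | one | 65 | 75 | 90 | 113 |
| One-sample | two | 42 | 48 | 55 | 68 |
| One-sample | one | 33 | 38 | 45 | 57 |

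Only the two-sample, two-sided, 80% setting gives 82.

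**What is at risk if 10.93 is the active-arm change.** The placebo changes below are illustrative and come from no section of the document. Evaluable per arm: 82 × 0.8 = 65.6; SD 22.28; two-sided 5%.

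| Placebo change (mm) | Between-arm difference (mm) | Power | Needed per arm after dropout for 80% |
|---|---|---|---|
| 0 | 10.93 | 80% | 83 |
| 2 | 8.93 | 63% | 123 |
| 3 | 7.93 | 53% | 155 |
| 5 | 5.93 | 33% | 278 |

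**Precision, which needs no assumed effect.** The 95% CI half-width for the difference in mean change is t × 22.28 × √(2/n).

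- 66 completers per arm: 1.978 × 22.28 × √(2/66) = 7.7 mm
- 82 per arm, the ITT set with imputed values taken at face value: 1.975 × 22.28 × √(2/82) = 6.9 mm

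**Allocation.** 2 × 82 = 164, so 164 is the total implied by 2.8.6. Read literally, 164 in each group would be 2 × 164 = 328.

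**The case against.** The strongest reply is that these are slips of wording in an exploratory trial. The two-sample formula returns 82 for whatever quantity is entered as 10.93, including a one-arm change entered by mistake. The back-calculation therefore shows how the figure was used, not what the cited research reported. The document's own cues, a hypothesis on Δ1 and Δ2 and a pooled SD, favour a between-arm value loosely described. All of this stands, and it limits the point to what the text says.

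A reader might go on to infer that the trial rests on the effect of a different treatment. The document does not establish this, because SDT is never defined and may be a mislabel. Borrowing would also be no defect in itself: the introduction says that no RCT of UCHA in CHHF has been done, and 2.8.6 discloses that the figures come from prior research.

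A reader might also infer that a claim of 80% power fails. The document makes no such claim. The 80% is reconstructed here, and the stated aims are to estimate efficacy and to support the power calculation of a later trial. The hypothesis display, which could show sidedness, is missing from the text at hand. Because the ITT analysis keeps all randomized subjects by carrying the last observation forward, a reduction to 66 per arm describes completers, not the planned ITT set. At 82 per arm and a true 10.93 mm difference, power would be about 88%.

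None of this removes the need for correction. The group name is wrong in two operative sentences, the description of 10.93 does not match its use, and the two statements of size contradict each other.

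**Conclusion.** The point holds as an error of labelling and internal consistency. SDT is not an arm of this trial; 10.93 mm is worded as a one-group difference but enters the calculation as a between-arm one; and 2.4 conflicts with 2.8.6 on the number per group. The reconstruction assumes a two-sided 5% level, 80% power and division by 0.8 for dropout.

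It would be going too far to say that 82 is miscalculated or that the trial is too small. The figure reproduces, and whether 10.93 was a between-arm or a within-arm result cannot be settled without the cited study. The power losses tabulated above apply only if it was within-arm and placebo patients improve. Nor is 328 a plausible intended size: the same sentence speaks of a total, and 164 is exactly twice 82.

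Changing the group name in 2.8.7.1 would not be enough. A paired t test is attached to that comparison, and UCHA and placebo patients are independent groups.

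**What to change.** - **Section 2.8.6:** say what SDT is. State whether 10.93 mm with SD 22.28 mm is a between-arm difference in change (Δ1 − Δ2), and give the alpha, sidedness and power actually used.
- **Section 2.8.6, if 10.93 mm is a within-arm change:** say that the calculation assumes no placebo change, and justify 82 per arm on precision instead, using the half-widths of about 7.7 mm (66 completers per arm) and 6.9 mm (82 per arm).
- **Section 2.8.7.1:** name the comparison as UCHA versus placebo and replace the paired t test by a test for independent groups.
- **Section 2.4:** write 82 per group, 164 in total.

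These are text corrections and need no extra patients. Recruitment is under way (72 enrolled according to section 3.1), so they should be made before unblinding. The cost is that the stated basis for the sample size may become less favourable.
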